##### tDCS adverse effects

Participants will be monitored for side effects of Active/Sham tDCS treatment using a tDCS Adverse Effects Questionnaire adapted from Brunoni et al. [25]. Following each treatment session, participants will be asked to record any side effects related to tDCS. Each item is measured on a 4-point scale (0=absent; 1=mild, 2=moderate, 3=severe).

##### Treatment Acceptability Questionnaire

The acceptability of tDCS as a healthcare intervention will be assessed using a Treatment Acceptability Questionnaire developed for the purpose of this study. The questionnaire draws from the work of Sekhon et al. [26] who outlined acceptability measurement methods for different stages of healthcare research based on a theoretical framework of acceptability. The questionnaire has 7 items. Each item is measured on a 3-point scale (1=not satisfied at all, 2=neutral, 3=very satisfied) with corresponding emojis. Participants will be asked to complete the questionnaire after the last tDCS session.

#### Additional measures

##### Trait impulsivity

To account for the effects of trait impulsivity on the outcome measures, the *Barratt Impulsiveness Scale version 11 (BIS-11)* [27] will be completed by each participant once at baseline, using the version adapted for use in people with IDD [28, 29]. This is a 30-item scale and each item is measured on a 4-point Likert scale (1=almost never, 2=sometimes, 3=often/a lot, 4= almost always/always). The first two points are denoted with dotted bars and the last two with solid bars for ease of reference. BSI-11 scoring yields a total score out of 120, and subscores for three higher order factors (attentional, motor and non-planning).

### Participant timeline {13}

Figure 1 outlines the proposed study procedure. Eligible participants will have a baseline clinical visit to confirm eligibility criteria and patient capacity, verify severity of aggressive behaviours, and obtain informed consent from participant or designated substitute decision-maker. Once enrolled, participants will be randomised into one of two study arms using a 1:1 allocation ratio. Participant blinding will be maintained but the research team will be unblinded to study arm.

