### Concealment mechanism {16b}

The allocation sequence will be communicated to the research assistant or trial coordinator after the completion of baseline measures including BPI-S, BIS-11 and MOAS.

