## Assignment of interventions: blinding

### Who will be blinded {17a}

This a single-blinded study where participants will be blinded to treatment allocation. Professionals who complete MOAS and BPI-S will also be blinded to treatment allocation. To minimise bias, the principal investigator and research assistant will be initially blinded to the allocation sequence. This will be generated by a Queen’s University independent faculty member who is not involved in the study, and then communicated to the research assistant administering the intervention after the completion of baseline measures. It is anticipated that having the research assistant unblinded is unlikely to introduce assessment bias since all the study questionnaires will be completed by the participants and professionals involved in their care, who will be blinded to the treatment allocation. Participants will only be unblinded to the treatment allocation if they developed a serious adverse reaction such as self-harm or serious violence. To assess the robustness of blinding, participants will be asked to guess their treatment allocation after the last tDCS session.

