### Procedure for unblinding if needed {17b}

As the study is single-blinded, the treatment administrator will always know what treatment arm the participants are in, so that in the event of an emergency, administrators can immediately unblind the participant and/or emergency personnel.

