### Interim analyses {21b}

Interim analysis will be conducted once half (30) of the participants have been recruited. Study team members will perform this interim analysis. Stopping rules include: withdrawal of consent, development of a coincidental health problem/illness, exacerbation of aggressive behaviours expressed as a report of a serious violent incident and/or an increased incidence of self-harm or self-injurious behaviour. The principal investigator and the Research Ethics Board will make the final decision about early trial termination.

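### The timeline section unblinds the research team, while the concealment and blinding sections give allocation only to the assistant or coordinator; reconcile them and analyse coded arms

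*Protocol article*

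**What the plan says.** The Protocol article describes a single-blind trial and deals with knowledge of allocation in several places.

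- **Participant timeline {13}:** "Participant blinding will be maintained but the research team will be unblinded to study arm". No role within the team is excepted, and no end date is given.
- **Concealment mechanism {16b}:** "The allocation sequence will be communicated to the research assistant or trial coordinator after the completion of baseline measures".
- **Who will be blinded {17a}:** "the principal investigator and research assistant will be initially blinded to the allocation sequence". The sequence is produced by a faculty member outside the study and is "then communicated to the research assistant administering the intervention after the completion of baseline measures". On the raters: "Professionals who complete MOAS and BPI-S will also be blinded to treatment allocation".
- **Procedure for unblinding if needed {17b}:** "the treatment administrator will always know what treatment arm the participants are in". This is the stated basis for emergency unblinding.
- **Interim analyses {21b}:** "Interim analysis will be conducted once half (30) of the participants have been recruited", and "Study team members will perform this interim analysis".

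Three other sections matter. Under the discontinuation criteria {11b}, the trial investigators judge whether the intervention has made behaviour worse at trial level. The section on the data monitoring committee {21a} gives monitoring to the investigators' own management group and says that funds did not allow an independent committee. The section on non-adherence and missing data {20c} makes the choice between carry-forward and multiple imputation depend on the pattern of missingness.

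**The concern.** Two different rules are in force. One opens allocation to the research team. The other limits it to the assistant or coordinator and leaves the principal investigator's later status open. A reader cannot tell which the trial follows.

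This matters because several decisions after randomisation rest on judgement and not on a fixed numerical rule: how the interim data are read, whether behaviour has worsened enough to stop the trial, and which missing-data method applies. Someone who knows the arm can be influenced, without intending it, by the difference that is emerging. With no independent monitoring committee, keeping these people blinded is the main inexpensive safeguard that remains, and the timeline sentence gives it up. The document offers no reason why anyone other than the person operating the device should know the arm.

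**Working it through.** The point concerns roles and does not rest on a sample size, power or error rate. The check therefore sets the sections side by side.

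**Step 1. Who knows the arm after baseline, by section**

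| Section | Assistant or coordinator giving tDCS | Principal investigator | Rest of team |
|---|---|---|---|
| {13} | Knows | Knows, if counted in the research team | Knows |
| {16b} | Told after baseline | Not listed as a recipient | Not listed as recipients |
| {17a} | Assistant told after baseline | Blinded at first; later status not stated | Not listed as recipients |
| {17b} | Always knows | Not required to know | Not required to know |

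The assistant's column agrees throughout, apart from whether the coordinator is also told. The other two columns do not: {13} opens what {16b} and {17a} keep closed. The word *initially* in {17a} could be stretched to fit {13}, but only by assuming a later release to the principal investigator that no section describes.

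**Step 2. Who needs to know**

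The device operator must know the arm to deliver active or sham current. Emergency unblinding {17b} relies on that same person. One role therefore covers every stated need during treatment.

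**Step 3. Which discretionary tasks could be reached if {13} is followed**

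| Task | Section | Done by | Blinding status stated there |
|---|---|---|---|
| Interim analysis | {21b} | Study team members | None |
| Judging trial-level worsening | {11b} | Trial investigators | None |
| Data monitoring | {21a} | Group of trial investigators | None |
| Choosing carry-forward or imputation | {20c} | Not named | None |

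The interim falls at 30/60 = 0.5 of planned recruitment, which agrees with the half that the plan states.

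**Step 4. What is outside the exposure**

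Participants are blinded, and so are the professionals who rate MOAS (primary) and BPI-S {17a}. Increased self-harm in an individual participant is judged by caregivers {11b}, who are nowhere described as unblinded. The final decision on early termination is shared with the Research Ethics Board {21b}.

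**Step 5. Who could hold a code**

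{17a} says an independent faculty member generates the sequence. Implementation {16c} says a member of the research team other than the principal investigator does so. These two statements must agree before anyone can serve as an independent code holder.

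**The case against.** The strongest reply is that {13} is a loose summary sentence in a section about the visit schedule, while the sections written to describe concealment and blinding are narrower and should govern. The trial is openly single-blind, and a condensed article may leave the blinding of analysts to a fuller document.

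Much of this stands, and it rules out stronger readings that a reader might infer.

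- *That the whole team certainly works unblinded.* This rests on {13} alone. {16b} and {17a} name only the assistant or coordinator as recipients, and no section says that this person runs the interim analysis or chooses the missing-data method.
- *That the final analysis is unblinded.* The final analyst is not named, and that person's blinding is neither affirmed nor denied.
- *That the primary outcome is rated with the arm known.* {17a} says the MOAS and BPI-S raters are blinded. {16c} speaks loosely of the assistant or coordinator completing outcome measures, but {17a} says explicitly that the questionnaires are filled in by participants and by blinded professionals.
- *That all stopping decisions lie with unblinded staff, or that an apparent benefit could end the trial early.* Caregivers and the Research Ethics Board have stated parts. The listed stopping grounds are withdrawal of consent, illness and behavioural worsening; no efficacy stop is stated.
- *That looking at the interim by true arm is itself an error.* Judging whether the intervention worsens behaviour {11b} may require knowing which arm is active. The weakness is that the study team does the looking.

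The reply does not remove the point. The sentence in {13} is an affirmative rule, not an omission, and it conflicts with {16b} and {17a}. The defence in {17a} answers only the risk that an unblinded assistant biases the questionnaires. It does not address interim review, monitoring or analysis choices.

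**Conclusion.** The point holds as a contradiction with a practical consequence. {13} unblinds the research team. {16b} and {17a} release allocation only to the assistant or coordinator and leave the principal investigator's later status undefined. {17b} needs only the person giving tDCS to know.

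If {13} is taken literally, those doing the interim analysis at 30 of 60, those judging trial-level worsening and monitoring data, and whoever chooses the missing-data method *can* know the arm. Whether they *will* depends on which section is followed and on who does each task, and the document settles neither.

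The size of any bias cannot be derived from the document. The risk lies in the conduct of the trial and in analysis decisions, not in the rating of MOAS or BPI-S. This is an inexpensive improvement worth making, and it does not by itself undermine the primary comparison.

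**What to change.** 1. Reword {13} to agree with {16b}, {17a} and {17b}: only the person delivering tDCS knows allocation. State in {17a} that the principal investigator and those analysing the data stay blinded until analysis decisions, including the missing-data method, are locked.
2. Run the interim and final analyses on arms coded A/B, with the code held by the independent faculty member described in {17a}. Align {16c} with {17a} on who generates the sequence, so that the code holder is clearly outside the team.
3. Allow the code to be disclosed, for example to the Research Ethics Board, when a harm judgement needs the true arm, and record each disclosure. This leaves the stopping criteria themselves unchanged.

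The cost is wording and one coded variable. There is one small practical downside. The adherence section {11c} has the principal investigator supervise the initial participant sessions directly. That supervision would have to take place without sight of the device setting, or those participants would be recorded as exceptions to the blinding.

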**Fig. 1 Fig1:**
[figure not shown]
Trial CONSORT diagram. Stop signal task (SST), Behavior Problems Inventory (BPI), Barratt Impulsiveness Scale version 11 (BIS-11), Modified Overt Aggression Scale (MOAS)

Participant healthcare records will be examined to obtain information concerning the diagnosis of IDD, demographics, number and duration of admissions to psychiatric institutions, and current psychotropic medication regime. A member of staff at the participant’s residence with good professional knowledge of the participant will be asked to complete the BPI and MOAS at baseline and 1 week after the last tDCS stimulation. At baseline, participants will be asked to complete the modified BIS-11, and SST. Three tDCS sessions will be delivered over three successive days (one session daily). Participants will be asked to repeat SST at the end of the third session (Fig. 1). Additionally, a tDCS adverse effects questionnaire will be administered following each tDCS treatment to detect adverse effects. At 1 week and also 1 month following the third and final treatment, participants will complete the BPI and MOAS and will be debriefed to unblind them to treatment arm.

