### Provisions for post-trial care {30}

Patients will be informed what arm (treatment or sham) they were allocated to at the end of the study. They will also be advised to contact the study's principal investigator should they experience any adverse effects following each session. Additionally, participants will continue to receive usual care at the discretion of the treating psychiatrist or care team. It usually involves a combination of behavioural approaches, psychosocial interventions, and psychotropic medications.

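### The participant timeline, read literally, unblinds participants at 1 week, in conflict with three other statements, and puts the blinding of the day-38 ratings at risk

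*Protocol article*

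**What the plan says.** Four statements in the protocol bear on when a participant learns the allocation.

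- **Participant timeline {13}, text under Fig. 1.** One time phrase governs two actions: "At 1 week and also 1 month following the third and final treatment, participants will complete the BPI and MOAS and will be debriefed". The purpose of the second is explicit: participants "will be debriefed to unblind them to treatment arm".
- **Participant timeline {13}, opening paragraph.** "Participant blinding will be maintained but the research team will be unblinded to study arm". No end point is given.
- **Provisions for post-trial care {30}.** "Patients will be informed what arm (treatment or sham) they were allocated to at the end of the study".
- **Who will be blinded {17a}.** "Participants will only be unblinded to the treatment allocation if they developed a serious adverse reaction such as self-harm or serious violence".

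On the rater, Outcomes {12} makes the MOAS, the primary outcome, an informant scale filled in by care staff at baseline, day 10 and day 38. Section {17a} says that the professionals who complete the MOAS and BPI-S are blinded. The text under Fig. 1 has residence staff complete both scales at baseline and 1 week only, and names the participants as completing them at 1 week and 1 month.

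**The concern.** A sham control protects the comparison only while the people whose behaviour or judgement produces the outcome do not know the arm. On its plain grammar the timeline sentence ends participant blinding at day 10, with one of the two post-treatment MOAS and BPI-S ratings still to come. The primary outcome is a judgement-based scale of behaviour. A participant who knows the arm may behave differently, or may tell the member of staff who will do the last rating. A difference at day 38 could then partly reflect expectation and not stimulation.

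The sentence is also an operational instruction. Under {16c} and {17b} the person who gives the treatment knows the arm and also handles the outcome measures. Someone working from the timeline could disclose the allocation on day 10, and that cannot be undone.

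**Working it through.** **Step 1: set the statements side by side.**

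| Section | When the participant learns the arm |
|---|---|
| {13}, text under Fig. 1 | At 1 week and at 1 month, read literally |
| {13}, opening paragraph | Blinding maintained, no end stated |
| {30} | End of the study |
| {17a} | Only after a serious adverse reaction |

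If the timeline sentence means both contacts, it conflicts with the other three rows. If it means a single closing debrief, it agrees with {30} and fits the opening paragraph of {13}, but both it and {30} still conflict with the word *only* in {17a}, unless that word is confined to the period of follow-up. No reading reconciles all the statements as worded.

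**Step 2: days at risk.** There are three daily sessions, so if the first is on day 1 the last is on day 3. One week later is 3 + 7 = day 10, which matches {12}. The last rating is on day 38, and 38 − 10 = 28 days. Under the literal reading, participants know their arm for the whole interval before the second post-treatment rating. The day-10 rating is unaffected if the debrief follows it.

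**Step 3: how the bias could reach the rating.**

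- *Staff informant rates at day 38, per {12} and {17a}.* The rater is blinded by rule. Bias can enter through the participant's own behaviour or through the participant telling the rater. The protocol describes no safeguard against the latter.
- *Participant completes the form at 1 month, per the text under Fig. 1.* An unblinded person rates the primary outcome directly. This contradicts {12}.

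**Step 4: illustrative size.** The protocol gives no figure for this bias, so there is none to reproduce. Assumptions:

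- baseline versus day 38 only, 30 per arm (N = 60, the recruitment target in {14}), two-sided α = 0.05;
- no true effect;
- an expectation bias of b SD between arms, and pre-post correlation r.

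The variance of a change score is 2(1 − r) in SD² units. The squared standard error of the between-arm difference in change is therefore 2 × 2(1 − r)/30, and

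λ = b² × 30 / [4(1 − r)] = N b² / [8(1 − r)].

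The false-positive rate is the probability that a noncentral F(1, 58, λ) exceeds the 5% critical value. Example: b = 0.3 and r = 0.5 give λ = 60 × 0.09 / (8 × 0.5) = 1.35.

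| b (SD) | r = 0.3 | r = 0.5 | r = 0.7 |
|---|---|---|---|
| 0.10 | λ 0.107, 6.2% | λ 0.150, 6.7% | λ 0.250, 7.8% |
| 0.15 | λ 0.241, 7.7% | λ 0.338, 8.8% | λ 0.563, 11.4% |
| 0.30 | λ 0.964, 16.2% | λ 1.350, 20.8% | λ 2.250, 31.4% |

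With 20% attrition (60 × 0.8 = 48 completers), the case b = 0.3, r = 0.5 gives λ = 48 × 0.09 / 4 = 1.08 and 17%.

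**The case against.** The strongest defence is that this is loose drafting. A participant can be unblinded only once, so the sentence cannot be meant in full for both visits. One debrief closing the follow-up is a natural reading, and it agrees with {30} and the opening of {13}. The *only* in {17a} stands in a section about blinding during the trial and leads into emergency unblinding, so it can be read as silent on disclosure afterwards. This has force: the documents do not show that the investigators chose to unblind before day 38. It does not remove the defect, because the literal instruction is there to be followed.

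A reader might go further and infer that the day-38 MOAS becomes open-label, or that the raters would learn the arm. The documents do not support that. Sections {12} and {17a} make the rater a blinded member of care staff, and telling a participant does not in itself tell the rater. Nor does any section say that participants live with their raters. The protocol speaks of staff at the residence, and {14} expects most participants to come from the community. Leakage is possible but not established.

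A single inflation figure would also be too strong. The upper values in the table take a bias of 0.3 SD, the same number as the effect size in {14}. They apply to a day-38 comparison, whereas {20a} describes a pre-post analysis and does not say which follow-up time is primary.

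**Conclusion.** The point holds as a contradiction on when allocation is disclosed, with a consequence for the primary outcome if the timeline is followed as written. Participants would then know their arm for about 28 days before one of the two post-treatment MOAS and BPI-S ratings. The blinding of that rating is put at risk; it is not shown to be lost. The risk is indirect if the blinded staff informant rates at day 38, and direct if the participant does.

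The false-positive range of about 6% to 31% against a nominal 5% is illustrative. It rests on an assumed bias of 0.1 to 0.3 SD, an assumed correlation of 0.3 to 0.7, all 60 participants rated, and day 38 analysed alone. The conclusion does not depend on it: the sections disagree, and early disclosure cannot be reversed.

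**What to change.** 1. In the text under Fig. 1 in {13}, separate the debrief from the assessments. State that routine disclosure of allocation happens once, only after that participant's day-38 MOAS and BPI-S are completed.
2. In {17a}, reword the sentence so that the emergency unblinding already provided for is the only exception before that point.
3. In {30}, define the end of the study for this purpose in the same terms.
4. In {13}, state that the blinded care-staff informant completes the day-38 MOAS and BPI-S, in line with {12} and {17a}.

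The cost is a few sentences. For any participant who would otherwise have been told at 1 week, the debrief moves about 4 weeks later. No visits, measures or participants are added. Recruitment had begun by the date of this protocol version, so the investigators should also record whether any participant was told the allocation before day 38, and report those ratings as such.

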The study will recruit participants [henceforth, the term ‘participant’ will be used throughout the protocol to refer to individuals with IDD undergoing the intervention] from intellectual developmental disability services in the Kingston area (or Southern Ontario Region). Posters will be placed publicly at Resource Centres in Kingston, and community living spaces where people with IDD reside. Participants will be identified by their psychiatrist, caregiver, or support worker. Capacity to consent to participate in research will be determined by the individual’s treating psychiatrist. Individuals designated to identify potential participants will ask prospective participants or their substitute decision-maker to complete a hospital “consent to be contacted for research” form. Study personnel (a research assistant or study coordinator) will then contact the individuals who have already consented to be contacted for research purposes either in person at the health service, by phone, or by email. If an individual is unable to provide consent, their substitute decision-makers will be approached. Study personnel will ensure that potential participants have not opted-out or withdrawn their consent or provided consent to be contacted for research purposes before initiating contact with participants or their substitute decision-makers.

Designated study personnel will review or read over the consent with the participant or their substitute decision-maker and answer any questions they have. Individuals must be able to understand that participation is completely voluntary and they can withdraw consent at any time and without giving a reason. To minimise coercion in the consenting process, the participant letter of information has been adapted to a grade 3 reading/comprehension level. The letter provides information about the side effects of tCDS using a simple language with visual aids. For example, it explains about tingling as follows: “A lot of people feel a tingling feeling under the pads. It should not hurt. This is felt when the electricity is turned on and just after. It is not scary.”

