### Outcomes {12}

#### Primary outcome measure

##### Aggression

The *Modified Overt Aggression Scale* (MOAS) [20] will be used as a repeated measure to assess aggressive behaviours at baseline, 1 week (day 10), and 1 month (day 38) following the last tDCS treatment. MOAS is an informant-rated scale which will be completed by a member of care staff who have professional knowledge of the participant. MOAS has four domains (Verbal Aggression, Aggression Against Property, Autoaggression, and Physical Aggression) which are weighted and each rated on a 5-point scale (0–4). Scoring of MOAS yields weighted scores, total and by domain. MOAS is considered to be a reliable measure of aggressive behaviours in people with IDD [21].

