### Sample size {14}

A power calculation conducted using repeated measures ANOVA (G*Power) yielded a total sample size of 50 participants (effect size=0.30, power=95%, *α* = 0.05). To allow for an attrition rate of 20%, we will aim to recruit 60 participants (30 per arm). These parameters were based on other studies involving the use of tDCS to modulate cognitive and behavioural functioning [30, 31]. Indeed, Minarik and colleagues [30] recommended small to intermediate effect sizes (between *d*=0.4 and *d*=0.5) for tDCS studies. We opted for an effect size of *d*=0.3 to improve precision. Furthermore, sample size calculation by Cosmo and colleagues [31] yielded 25 participants per arm for a power of 80% and bidirectional type I error probability of 0.05%. To allow for an attrition rate of 20%, a final sample size of 60 was considered sufficient by Cosmo and colleagues to detect a 50% difference in performance on the inhibitory control task in the active tDCS group, and a 10% difference in the sham tDCS group. While we acknowledge the importance of accounting for clustering by in-patient/care home, given our clinical experience, we anticipate that most of the participants will be recruited from the community. Furthermore, given the special nature of the population in this study and the funding constraints, it would be unrealistic to aim to recruit larger numbers. Nevertheless, we believe that the sample size of 30 participants per study arm is sufficiently large to detect differences between the effects of active and sham tDCS.

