### Implementation {16c}

A member of the research team other than the principal investigator will generate the allocation sequence. The study’s research assistant or coordinator will enrol participants, complete the outcome measures, and administer the interventions.

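### The protocol contradicts itself on who completes the MOAS at follow-up, and on whether that rater is still blinded

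*Protocol article*

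**What the plan says.** Four sections of the protocol article say who completes the primary outcome.

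- **Outcomes {12}, Aggression:** "MOAS is an informant-rated scale which will be completed by a member of care staff who have professional knowledge of the participant". The measure is scheduled at baseline, day 10 and day 38. The same section calls the Behavior Problems Inventory Short Form (BPI-S) informant-rated.
- **Participant timeline {13}** (text after Figure 1): a staff member at the residence "will be asked to complete the BPI and MOAS at baseline and 1 week after the last tDCS stimulation". The same paragraph ends: "At 1 week and also 1 month following the third and final treatment, participants will complete the BPI and MOAS". That sentence continues into the debrief: "participants will complete the BPI and MOAS and will be debriefed to unblind them to treatment arm".
- **Implementation {16c}:** the "research assistant or coordinator will enrol participants, complete the outcome measures, and administer the interventions".
- **Who will be blinded {17a}:** the professionals who complete MOAS and BPI-S are blinded. The unblinded research assistant is judged unlikely to cause assessment bias because "all the study questionnaires will be completed by the participants and professionals involved in their care, who will be blinded to the treatment allocation".

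The consent section {26a} fixes the meaning of the word participant: it "will be used throughout the protocol to refer to individuals with IDD undergoing the intervention".

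**The concern.** MOAS is a judgement-based scale and the trial is single-blind, so the protection of the primary outcome rests on who fills in the form and what that person knows. The design in {12} and {17a} is sound: care staff who do not know the arm. Two other sections, read as instructions to site staff, lead elsewhere. One gives the follow-up forms to the participant. The other gives completion of the measures to the person who delivers the stimulation.

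The timeline adds a second route to unblinded rating. It attaches the debrief that reveals the arm to both the 1-week and the 1-month visit. Someone told the arm at 1 week could then rate at 1 month, or pass the information to the care-staff rater before that rating.

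Ratings collected under the wrong rule cannot be repaired in the analysis. Nor is this a detail left to a fuller document: the article itself states who rates and who is blinded, and Plans for assessment and collection of outcomes {18a} refers back to the timeline for the whole collection plan.

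**Working it through.** The protocol gives no figure to reproduce here, so the check sets the sections side by side.

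**Step 1. Who completes MOAS at each visit, as written**

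| Visit | Outcomes {12} | Timeline {13} | Implementation {16c} | Blinding {17a} |
|---|---|---|---|---|
| Baseline | care staff | residence staff | research assistant or coordinator (allocation not yet known) | blinded professionals |
| 1 week (day 10) | care staff | residence staff, and also participants | research assistant or coordinator (allocation known) | blinded professionals |
| 1 month (day 38) | care staff | participants; no staff named | research assistant or coordinator (allocation known) | blinded professionals |

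Three types of rater appear, and the sections conflict at both follow-up visits.

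**Step 2. Can the timeline's participants mean the informants?** No. The definition in {26a} covers the whole protocol. The timeline paragraph itself also keeps the two groups apart at baseline: staff complete the informant scales, while participants complete the Barratt scale and the Stop Signal Task.

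**Step 3. Does the research assistant know the arm at follow-up?** Yes. Concealment mechanism {16b} and {17a} release the allocation once baseline measures are complete. Procedure for unblinding {17b} says the person giving treatment always knows the arm. Timeline {13} describes the research team as unblinded. So {16c}, taken at its word, removes the premise that {17a} relies on.

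**Step 4. When are participants unblinded?** Timeline {13} places it at 1 week and 1 month. Provisions for post-trial care {30} places it at the end of the study. {17a} restricts it to a serious adverse reaction. These three do not agree, and the first allows unblinding before the day-38 rating.

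**Step 5. What each problem does to the analysis.** Statistical methods {20a} define success as a greater MOAS reduction in the active arm than in the sham arm. Let A and S be the true mean changes in the active and sham arms.

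- Staff-to-participant switch that shifts scores by c in both arms: (A + c) − (S + c) = A − S. The shift enters the time effect and cancels in the contrast. What remains is extra noise and doubt about what a self-completed informant scale measures.
- Rater who knows the arm and scores the active arm lower by b: (A − b) − S = (A − S) − b. The bias passes in full into the primary contrast.

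The document gives no MOAS standard deviation, no agreement between raters and no estimate of b, so neither the noise nor the bias can be sized from it.

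**The case against.** The strongest defence is that the intention is clear. The two sections that deal specifically with the scale and with blinding both point to blinded care staff. {16c} is a one-line summary that does not name MOAS, and completing the measures may only mean seeing that they get done; Strategies to improve adherence {11c} speaks of administering the questionnaires. The debrief may likewise have been meant only for the last visit. This stands as far as it goes: a reader might infer that the person giving the stimulation will score the primary outcome, and the document does not establish that. It does not rescue the timeline, where the definition of participant excludes the benign reading and no staff rater is named at 1 month.

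Three stronger readings are tempting but unsupported.

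- *That a change of rater biases the treatment effect.* A shift common to both arms largely cancels in the group-by-time contrast (step 5). The cancellation is exact only if the shift is additive and equal in the two arms.
- *That the bias can be stated as a share of the planned effect size of 0.3.* This would divide an assumed rater bias by the planning figure; nothing in the protocol supports the assumed value.
- *That many participants will have no informant, so an eligibility criterion is needed.* The sample size section does say "we anticipate that most of the participants will be recruited from the community". But Recruitment {15} lists clinics, inpatient units and community residential homes, and {26a} has participants identified by their psychiatrist, caregiver or support worker. A shortage of informants is speculation. A new criterion would also not clearly be cheap, since Plans for communicating protocol amendments {25} requires ethics approval for eligibility changes.

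**Conclusion.** The contradiction is real, concerns the primary outcome and should be fixed. Followed literally, the timeline yields self-rated follow-up scores and permits unblinding before the last rating. Followed literally, {16c} yields follow-up ratings by someone who knows the arm and contradicts the argument in {17a} against assessment bias.

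The conclusion is limited to what the text permits. It does not show that unblinded rating was intended or will occur. Of the two consequences, unblinded rating is the one that could bias the group-by-time contrast; a rater change common to both arms mainly costs precision and validity. No magnitude is claimed, and the conclusion needs none: it rests only on the wording of the sections compared above.

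**What to change.** Reconcile Outcomes {12} (both the MOAS and BPI-S paragraphs), Participant timeline {13}, Implementation {16c} and Who will be blinded {17a} to one rule: MOAS and BPI-S are completed at baseline, day 10 and day 38 by a care-staff informant who is blinded to allocation, and by the same informant each time where possible.

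- **Timeline {13}:** in the sentence "participants will complete the BPI and MOAS and will be debriefed to unblind them to treatment arm", name that informant as the rater in place of the participant. Name the informant for the 1-month visit as well as for baseline and 1 week.
- **Timeline {13}, debrief:** place the routine debrief and unblinding after the day-38 rating, consistent with {30}, and align the wording of {17a}. Changing the rater alone would leave the 1-week unblinding in place. Emergency unblinding under {17b} is not affected.
- **Implementation {16c}:** replace completion of the outcome measures with distributing and collecting the forms and administering the Stop Signal Task.

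Asking informants at day 38 to guess the allocation would be a useful check, but it is optional.

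Cost: minor wording changes and the practical effort of keeping the same informant across three visits. The design, sample size and analysis do not change.
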